# NUrse-led COntinuum of care for people with Diabetes and prediabetes (NUCOD) in Nepal: study protocol for a cluster randomized controlled trial

**DOI:** 10.1186/s13063-020-04372-5

**Published:** 2020-05-29

**Keywords:** Continuum of care, Diabetes, Prediabetes, Randomized controlled trial, Implementation

## Abstract

**Background:**

The purpose of this study will be to improve diabetes prevention, access to care and advocacy through a novel cost-effective nurse-led continuum of care approach that incorporates diabetes prevention, awareness, screening and management for low-income settings, and furthermore utilizes the endeavor to advocate for establishing a standard diabetes program in Nepal.

**Methods:**

We will conduct a two-arm, parallel group, stratified cluster randomized controlled trial of the NUrse-led COntinuum of care for people with Diabetes (*N*_1_ = 200) and prediabetes (*N*_2_ = 1036) (NUCOD) program, with primary care centers (9 outreach centers and 17 government health posts) as a unit of randomization. The NUCOD program will be delivered through the trained diabetes nurses in the community to the intervention group and the outcomes will be compared with the usual treatment group at 6 and 12 months of the intervention. The primary outcome will be the change in glycated hemoglobin (HbA1c) level among diabetes individuals and progression to type 2 diabetes among prediabetes individuals, and implementation outcomes measured using the RE-AIM (reach, effectiveness, adoption, implementation and maintenance) framework. Outcomes will be analyzed on an intention-to-treat basis.

**Discussion:**

The results of this trial will provide information about the effectiveness of the NUCOD program in improving clinical outcomes for diabetes and prediabetes individuals, and implementation outcomes for the organization. The continuum of care model can be used for the prevention and management of diabetes and other noncommunicable diseases within and beyond Nepal with similar context.

**Trial registration:**

ClinicalTrials.gov, NCT04131257. Registered on 18 October 2019.

## Background

Prevalence of type 2 diabetes (hereafter, diabetes) has been rising like a silent epidemic in Nepal, similar to other developing countries. A systematic review and meta-analysis reported a pooled prevalence of type 2 diabetes of 8.4% (95% CI: 6.2–10.5%) [1]. It is estimated that between 1990 and 2010 the burden of diabetes increased by about 89% in Nepal [2].

The most recently published Disease Control Priority-3 (DCP-3) systematically reviewed available interventions for diabetes in resource-limited settings, and strongly recommended the following interventions based on their cost-effectiveness and feasibility: targeted (two-step) screening for both prediabetes and diabetes; blood pressure control among people with diabetes; lifestyle interventions to prevent diabetes among high-risk individuals; and good glycemic control along with smoking cessation and foot care. Those interventions, ranging from case detection to prevention of diabetes among those at high risk, to diabetes management and to screening for preventing diabetes complications, have been extensively tested for efficacy and cost-effectiveness. However, the DCP-3 pointed out two knowledge gaps: little evidence for the testing of the effectiveness of those interventions in low-income settings; and a lack of implementation-oriented research for adopting and scaling up those interventions. This is compounded by the fact that a chronic disease like diabetes needs a structured, well-concerted comprehensive approach comprising continuum of care prevention activities, timely screening, standard clinical management and self-management skills for lifestyle modification rather than segregated interventions. Nurse care coordinators have been found to improve patient and health service outcomes, particularly when they frequently interacted with the patients, conducted follow-up with monitoring and education of the disease and behavioral changes, and were involved in transition care [3–7]. However, they often focused on specific components rather than the full spectrum of the continuum of care for the patient. Also, studies are rarely conducted in low-income countries.

The Dhulikhel Hospital (DH) system is a community-oriented, nongovernmental health system with an extensive network of 21 rural community-based outreach centers. The DH system provides a well-suited setting for innovating a continuum of care for people with diabetes. In this trial, we aim to develop and implement a “continuum of care” program with trained nurses as the nucleus. The nurses, along with the community health worker, will coordinate and implement a composite of the DCP-3-recommended individual intervention components for the low-income setting: leading community awareness campaigns; organizing diabetes screening events; linking diabetic patients to comprehensive clinical care (which will have been structured based on standard guidelines); and ensuring treatment adherence and self-management through regular community-based group counseling programs. The primary objective of this study is to examine the effectiveness of this comprehensive intervention in promoting the health of the people with diabetes and prediabetes, and the secondary objective is to examine whether the nurse coordination will promote the implementation of the evidence-based, DCP-3-recommended interventions. We hypothesize that the NUrse-led COntinuum of care for people with Diabetes and prediabetes (NUCOD) program will improve both clinical outcomes as well as implementation outcomes, compared with diabetes usual care in low-income settings.

## Methods

### Design

This study will be a two-armed, parallel group, stratified cluster randomized controlled trial (RCT) of the NUCOD program (Fig. 1), with the health center as a unit of randomization. We will use a computer-generated list of random numbers to randomize health centers stratified by Kathmandu University (KU) outreach centers and government health posts, whereby all patients from the same health center will be allocated to the same group. The study will be planned and implemented in concordance with the Consolidated Standards of Reporting Trials (CONSORT) cluster trial extension statement [8] and the Standards for Reporting Implementation Studies (StaRI) statement [9]. We plan to use the cluster design to reduce between-group contamination and spillover effects of the intervention as well as to align the design with the natural project implementation unit based on the cluster.

**Fig. 1 Fig1:**
[figure not shown]
Summary of the trial design for the NUCOD program. BMI body mass index, HbA1c hemoglobin A1c (aka glycated hemoglobin), NUCOD NUrse-led COntinuum of care for people with Diabetes and prediabetes

### Setting

The study will be conducted in 26 clusters: 9 outreach centers (Bahunepati, Manekharka, Hindi Health, Baluwa, Bolde Phediche, Dapcha, Kartike Deurali, Salambu and Dhunkharka Health Centers) of Dhulikhel Hospital, Kathmandu University Hospital and 17 government health posts located in the adjoining catchment areas purposively selected from the Kavrepalanchowk and Sindhupalchowk districts. The primary stratification variable, as well as the unit (cluster) of randomization and implementation, will be health clinics (outreach centers and health posts (HPs)). There will be 13 clusters per treatment arm (1:1 allocation ratio). Outreach centers are the small medical health facilities that offer basic and emergency care services in remote areas of Nepal. These centers are run by Kathmandu University Hospital. Similarly, health posts are government-run facilities that provide basic health care and preventive medication in remote rural areas of Nepal.

Kavrepalanchowk district located in Province 3 of Nepal consists of 13 municipalities: 6 urban and 7 rural municipalities with a total of 137 wards. The headquarter of this district is Dhulikhel municipality. A total population of 381,937 resides in this district; 62.51% live in the urban municipalities and 37.49% live in the rural municipalities. There is one 15-bed district hospital, 4 primary health care (PHC) centers and 86 HPs in the district [10]. Sindhupalchowk district, also located in Province 3 of Nepal, consists of 12 municipalities: 3 urban and 9 rural municipalities with a total of 103 wards. The headquarter of Sindhupalchowk district is Chautara. A total population of 287,798 resides in this district; 41.42% live in the urban municipalities and 58.58% live in the rural municipalities. There is one 15-bed district hospital, 3 PHC centers and 75 HPs in the district [10]. The maps of Kavrepalanchowk and Sindhupalchowk districts with the distribution of outreach centers and health posts are shown in Figs. 2 and 3.

**Fig. 2 Fig2:**
[figure not shown]
Map of Kavre District with outreach centers of Dhulikhel Hospital and government facilities. ORC outreach center

**Fig. 3 Fig3:**
[figure not shown]
Map of Sindhupalchowk District with outreach centers of Dhulikhel Hospital and government facilities. ORC outreach center

### Participants

#### Eligibility criteria for health centers/health posts

Outreach centers/health posts located in the Kavrepalanchowk and Sindhupalchowk districtsHave a nurse (staff nurse or auxiliary nurse midwife (ANM))

#### Eligibility criteria for participants

To resemble the real-world settings as much as possible, we will apply the minimum inclusion and exclusion criteria for the participants. Individual with confirmed pre-existing type II diabetes and prediabetes at the time of our screening (i.e., pre-existing diabetes or prediabetes) or with a confirmed diagnosis of type II diabetes or prediabetes after our community screening process (i.e., newly diagnosed diabetes and prediabetes), who is not planning to relocate outside the current place of living in next 2 years and is older than 18 years of age, will be eligible for project recruitment. People will be excluded if they: are not psychologically capable of communication; and are diagnosed with type 1 diabetes. Participants will be assessed for the risk of diabetes using the Indian Diabetes Risk Score (IDRS) [11]. Anyone identified as at risk will undergo a random finger-prick glucose test followed by the hemoglobin A1c (HbA1c) test. The diagnosis will be confirmed by an HbA1c level ≥ 6.5% for diabetes or between 5.7 and 6.4% for prediabetes [12].

### Screening and recruitment

The program will be rolled out with each outreach center/health post serving as the implementation unit. The program participants will be recruited through a community-based screening effort. Information regarding the screening event will be disseminated at the time of the awareness campaign. Trained diabetes nurses will screen the general population at the outreach center/health post, and those who screen positive will be referred to the DH diabetes clinic for further tests and for program recruitment if eligible for the study. All of the screening procedures including laboratory investigations and anthropometric measurements will be carried out at the respective centers, and all of the longitudinal data of patients will be entered into an electronic health record (EHR) system for data storage and management. Each participant will be assigned a unique identification number at the time of enrollment. All data collected as part of this study will be identified with this number. Research assistants (RAs) will be responsible for obtaining the signed informed consent form from the participants. On the consent form, participants will be asked whether they agree to use of their data should they choose to withdraw from the trial. Participants will also be asked for permission for the research team to share relevant data with people from the universities taking part in the research or from regulatory authorities, where relevant. This trial involves collecting biological specimens for storage.

Recruitment will be primarily through conducting diabetes awareness mass campaigns in the targeted sites of the two districts to achieve adequate participant enrollment. We intend to reach 50,000 people (approximately 2000 people at each of the 9 outreach centers and 17 health posts). Interested candidates will contact the study nurses, who will provide them with basic information about participation, including information on the screening process, time commitment and expectations associated with participation. Assuming 25% of those who are made aware of diabetes will participate in the screening (see later for the details of screening methods), we target screening 12,500 participants. The two-step screening approach will be used for the study after assessing the risk of diabetes among the individuals using the IDRS assessment tool. In the first step, anyone under risk will undergo a random finger-prick blood glucose test using Beurer glucometers [13]. A random blood sugar level of 200 mg/dl or higher will be considered positive for diabetes and a sugar level of 140–199 mg/dl will be considered positive for prediabetes [12]. In the second step, participants screened positive for a random blood glucose level will undergo a glycosylated hemoglobin (HbA1c) test. An HbA1c level between 5.7 and 6.4% will be considered positive for prediabetes and an HbA1c level of 6.5% or above will be considered positive for diabetes [12]. Participants with HbA1c level ≥ 5.7% will be invited to participate in the study. Based on the earlier quoted prevalences of 8.4% (95% CI: 6.2–10.5%) for diabetes [1] and 13% (95% CI: 11.8–14.5%) for prediabetes [14], we expect to identify 1050 (12,500 × 0.084) individuals with diabetes and 1625 (12,500 × 0.13) individuals with prediabetes for this study.

### Randomization

The 26 health clinics will be randomized 1:1 into the continuum of care group (intervention) and the usual care group (control), stratified by outreach center and health post. The usual care group includes those who continue managing their diabetes under the direction of their primary care providers, which is the most commonly used method for diabetes management in Nepal. The selection of the usual care group as a comparator is thus justified. A statistician otherwise not involved in the project will perform this group assignment at the cluster level with simple random selection with the R statistical program. Randomization will be done before participant recruitment. Outcome assessors will be blinded to the group assignment, but the nurses and patient participants will be aware of their group assignment. If blinding to the outcome assessor is accidentally broken, they will follow a standard protocol for reassessment of the patients at another time. Any violations of the study protocol will be recorded and reported to the Ethics Committee.

### Baseline assessment

At baseline, trained RAs will interview the participants using a standardized electronic questionnaire on CommCare, a mobile platform designed for data collection [15]. RAs will receive 2 weeks of training in data collection and ethical issues. The questionnaire will assess socioeconomic characteristics including age, sex, ethnicity, religion, marital status, annual income, education level and family history, and lifestyle factors including smoking, alcohol intake and physical activity. We will use the Global Physical Activity Questionnaire [16] to calculate the metabolic equivalent of task (MET) minutes per week. A weekly MET equivalent of 600 would represent 30 min of brisk walking five times per week or 15 min of running five times per week. We will use PrimeScreen questionnaire [17], a short diet assessment tool to assess the diet quality of the study participants. Body weight will be measured with minimum clothing and without shoes using an Omron Model HBF-400 scale and recorded to the nearest 0.1 pounds. The weighing scale will be calibrated to zero every day. Participants’ heights will be measured, without shoes, while the participants stand against a wall. Height will be measured using a tape measure and recorded to the nearest 0.1 cm.

Blood samples will be collected for HbA1c, low-density lipoprotein (LDL), high-density lipoprotein (HDL), triglycerides and total cholesterol at each respective health center where all the laboratory procedures will be carried out. Blood samples will be collected using evacuated blood collection tubes. Participants will be asked to fast overnight (8–14 h).

### Intervention: NUCOD program components

The intervention will be delivered by specially trained nurses from Dhulikhel Hospital (DH). The intervention has been developed based on our extensive literature review and the recommendations from the Disease Control Priorities-3 (DCP-3) as well as an analysis of local contexts in consultation with various stakeholders. The intervention will include the following components, logically sequenced as a continuum of care approach. Figure 4 presents the major program components. The nurses will act as the leader and coordinator for the implementation of all the program components:
*▪ Training of nurses*: by drawing from standard training manuals published by the International Diabetes Federation and American Diabetes Association, the project management team will first develop a protocol and content for the training of nurses for this program. This training protocol will be tailored to the context of Nepal and will include case studies and examples relevant to Nepal. The training will focus on clinical as well as case management skills. We will train 26 nurses (one for each site) into diabetes nurses using this training protocol.*▪ Community awareness campaigns*: the nurses will lead the organization of a mass campaign on diabetes in coordination with local newspapers, radio stations, youth groups, municipality offices, district health offices and other health facilities. The campaigns will, in particular, include a simple diabetes risk factor assessment tool to be adapted from the Type 2 Diabetes Risk Test (DRT) of the American Diabetes Association [18]. The campaign will encourage people with high risk to attend the screening program.*▪ Screening programs*: the nurses will organize screening programs for both diabetes and prediabetes for the community members on specific dates and sites, which will be communicated beforehand to the people in the locality. The screening will be done in coordination with the clinical biochemistry department of DH.*▪ Linkage to clinical care*: people who screened positive for diabetes and prediabetes (pre-existing as well as new) will be linked to the DH clinic by nurses, where they will be recruited into the program and will receive their group assignment. People assigned to the control group will follow the usual procedure, while those assigned to the intervention group will attend a 1-h nurse-led counseling session on diabetic care. The patients will be responsible for their medical costs (laboratory investigations and medicine), while people experiencing financial hardship can apply for charity care (free or at a reduced price) with guidance from the nurse. The assigned nurse will be responsible for determining their financial profile by reviewing the annual household income, applicable assets, available insurance coverage and confirmation of other sources of payment.*▪ Community follow-up counseling and support for the diabetic patients*: the nurse will organize diabetic patients into groups of 10 and arrange bimonthly meetings (each 2 h in length) in which the patients will be facilitated using the 5A framework (Assess, Advise, Agree, Assist and Arrange follow-up) to adopt a healthy lifestyle (dietary changes, physical activity, cessation of smoking, etc.) [19]. In addition to the lifestyle changes, the participants will also be facilitated to adhere to medical advice (timely follow-up, adherence to medications, etc.). The nurses will also coordinate with the diabetes clinic at the hospital to ensure that the clinical care and the community-level interventions complement each other. They will also have an electronic tablet that has all the details (laboratory results, behavioral parameters, anthropometric measures, etc.) of the participants so that the progress of the participants in these parameters can be recorded and assessed.*▪ Prevention programs for prediabetic participants*: in addition to the people with diabetes, the nurses will also form groups of prediabetes participants and will arrange monthly meetings to help facilitate the adoption of a healthy lifestyle using the Diabetes Prevention Program (DPP) curriculum. The DPP lifestyle intervention has been associated with significantly reducing the development of diabetes through its structured behavior-changing approaches [20]. A multidisciplinary team of dieticians and physical therapists will assist with the other components of the DPP program that are related to nutrition and physical activity.

**Fig. 4 Fig4:**
[figure not shown]
Intervention components of the NUCOD program. DH Dhulikhel Hospital, NUCOD NUrse-led COntinuum of care for people with Diabetes and prediabetes

The control group will receive the usual diabetic care, which includes the same hospital quality improvement for diabetic care as already mentioned, the follow-up services from the female community health volunteers (FCHVs) (but without the nurse coordination and supervision as in the intervention group) in addition to the usual care. FCHVs are the grass-roots level of community health workers in Nepal who play important roles in the implementation of community-based programs, including screening for high-risk cases, referring people to local health facilities and maintaining a record of health activities [21]. The program comparison of the intervention group versus the control group is summarized in Table 1.

**Table 1 Tab1:** Program components for the intervention versus control groups

	Intervention group	Control group
Community awareness campaigns led by trained nurses	x	x
Screening	x	x
Linkage to clinical care	x	
• Coordinated through the nurses	x	
• provided by FCHVs without involvement of the nurse		x
Improved quality of care at the hospital	x	x
Nurse-led counseling	x	
Community follow-up coordinated through the nurses	x	
Prevention program to prediabetics through the nurses	x	

*FCHV* female community health volunteer

### Outcome measures

We will examine both clinical outcomes and implementation outcomes as we hypothesize that the nurse-led continuum of care program will improve both health and the implementation of priority interventions in diabetes. The outcome measure will pertain to the individual participant level. The primary outcome for the diabetes group is the HbA1c level at 12 months from the intervention. The HbA1c level is indicative of the average level of blood glucose over the past 2–3 months [22]. The primary outcome for the prediabetes group is the incidence of diabetes at 12 months from the intervention.

The secondary outcomes are blood pressure, body mass index (BMI) and lipid levels. Also, the secondary outcomes include a series of implementation outcomes in the RE-AIM (reach, effectiveness, adoption, implementation, and maintenance) implementation framework [23–25]. We provide details on those measures in the following (see Table 2 for a summary).

**Table 2 Tab2:** Measures of outcome variables

	Assessment method	Assessor	Baseline	Midline (6 months)	End line (12 months)	Variable
**Clinical outcomes**						
*Primary outcome*						
Glycemic control (HbA1c)^a^ for diabetes	Blood sample	Biochemist	x	x	x	Continuous
Incidence of diabetes among prediabetes	EHR	RA/nurse		x	x	Binary
*Secondary outcomes*						
Blood pressure	Electronic monitor	RA/nurse	x	X	x	Continuous
Lipid profile	Blood sample	Biochemist	x	X	x	Continuous
Body mass index	EHR^b^	RA/nurse	x	x	x	Continuous

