#### Clinical outcomes

The clinicians from Dhulikhel Hospital outreach centers not otherwise associated with the project will measure HbA1c, lipid profiles, BMI and blood pressure when the participants visit the diabetic clinic at baseline, 6 months and 12 months.

HbA1c will be measured using Boronate affinity chromatography (Axis-Shield; Norway) [26], LDL and HDL using the elimination method (Dialab; Austria) [27], triglyceride using GPO-PAP (Dialab; Austria) [28] and total cholesterol using CHOD-PAP (Dialab; Austria) [29]. For each type of assay, the laboratory has quality control (QC) materials (using commercially available assayed and unassayed control material) from Bio-Rad Laboratories, USA. Each QC is run at least in duplicate. External QC is arranged by internationally recognized reference laboratories that distribute batches of samples of various concentrations for each assay. The laboratory performs the External Quality Assurance Scheme from an unknown assayed sample from the Department of Clinical Biochemistry CMC, Vellore, India for 23 routine parameters, 5 immunological parameters and HbA1c. Additionally, 5% of the blood samples will be obtained in duplicate and sent for testing of all parameters, blinded to the laboratory personnel.

The mean of three measurements of systolic and diastolic blood pressure, using a Microlife automatic blood pressure measuring device, will be adopted for analysis. Hypertension is defined as systolic blood pressure ≥ 140 mmHg or diastolic blood pressure ≥ 90 mmHg or taking antihypertensive medication [30]. Weight will be measured and recorded to the nearest 0.1 kg, without shoes and with minimum clothing, using an Omron Model HBF-400 scale. Height will be measured without shoes using a standard tape measure with participants standing against a wall for measurement, and recorded to the nearest 0.1 cm. The BMI will be calculated as weight in kilograms divided by height in meters squared. Overweight is defined as a BMI of 25 kg/m^2^ or higher and obesity is defined as BMI of 30 kg/m^2^ or higher based on international cutoff points [31].

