#### Implementation outcomes

The RE-AIM (Reach, Effectiveness, Adoption, Implementation, and Maintenance) framework will be implemented as follows:
*Reach* will be measured by the number of people participating in the program divided by the number of people eligible to be recruited into the program.*Effectiveness* will be represented by the clinical outcomes.*Adoption* at the patient level will be measured by the proportion of people adherent to the clinical advice in lifestyle and self-care—this will be measured by the self-reported Summary of Diabetes Self-Care Activities (SDSCA) scale [32] at baseline, 6 months and 12 months (the SDSCA measure is a brief self-report questionnaire that includes items assessing general diet, specific diet, exercise, blood-glucose testing, foot care and smoking) and, in addition, the Diabetes Treatment Satisfaction Questionnaire (DTSQ) [33] will be administered at baseline, 6 months and 12 months (the DTSQ is the most commonly used patient-reported outcome in diabetes trials, which reflects the patient’s perception of the treatment)—and at the clinic level will be measured by the proportion of health clinics successfully recruited into the program over the clinics eligible and approached to participate in the program.*Implementation* will examine the fidelity and quality of the program execution per protocol. To check program fidelity, we will select and train standardized patients (SPs) from the program participants with stable conditions—these SPs will serve as the “secret agents” and the sentry to assess program fidelity with a quality checklist through their routine encounters with the clinicians at the DH diabetes clinic and the nurses; the clinicians will be blinded to the status of the SPs; and the development of SPs and the checklist will follow the protocol we have developed in a separate study [34].*Maintenance* will not be assessed for the purpose of this study.

The hospital and program administrative system will collect a range of other information including detailed program costs, health service utilization and incidence of complications and comorbidities. All data will be entered and securely stored in the EHR, a secured online data capturing and management system developed for the study at the DH.

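### Table 2 lets an unblinded nurse classify incident diabetes from the EHR, and nothing ties this primary outcome to the scheduled HbA1c

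*Protocol article*

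**What the plan says.** The Outcome measures section states: "The primary outcome for the prediabetes group is the incidence of diabetes at 12 months from the intervention". Table 2 lists this outcome as "Incidence of diabetes among prediabetes", a binary variable assessed at 6 and 12 months, with the EHR as method and RA/nurse as assessor. The HbA1c row directly above reads "for diabetes Blood sample Biochemist", so the laboratory route is labelled for the diabetes cohort only. Lipids also have blood sample and biochemist. Blood pressure and BMI have RA/nurse.

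Two other sections describe who assesses outcomes:

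- Randomization: "Outcome assessors will be blinded to the group assignment, but the nurses and patient participants will be aware of their group assignment".
- Clinical outcomes: "The clinicians from Dhulikhel Hospital outreach centers not otherwise associated with the project will measure HbA1c, lipid profiles, BMI and blood pressure", and this happens "when the participants visit the diabetic clinic at baseline, 6 months and 12 months".

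A diagnostic threshold appears under Eligibility criteria for participants: "The diagnosis will be confirmed by an HbA1c level ≥ 6.5% for diabetes". Screening and recruitment repeats it. Both uses concern entry to the trial. Implementation outcomes describes the EHR as "a secured online data capturing and management system developed for the study at the DH".

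**The concern.** Table 2 names the nurse as a possible assessor of a primary outcome. The Randomization section says that every nurse knows the allocation and also that outcome assessors do not. Both cannot be true when a nurse fills the assessor role. The nurses at intervention sites also run the program under test, including the monthly prediabetes groups.

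The source is also unclear. If all study data go into the EHR, then EHR names a place of storage, not a measurement. A recorded diagnosis could rest on the scheduled HbA1c, on a test done between visits, or on a random glucose, since the first screening step calls 200 mg/dl or higher positive for diabetes. If diagnoses made between visits count, the arm with more contact has more chances to be diagnosed, which would raise its recorded incidence. An unblinded recorder could lower it. The two pull in opposite directions, so the net effect cannot be predicted.

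**Working it through.** **Side-by-side reading**

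| Item | Table 2 | Text |
|---|---|---|
| Incident diabetes (prediabetes cohort) | EHR; RA/nurse; 6 and 12 months | 12 months; no follow-up definition; assessors blinded, nurses not |
| HbA1c | Blood sample; biochemist; labelled for diabetes | Outside clinicians; all participants; baseline, 6 and 12 months |
| BMI | EHR; RA/nurse | Outside clinicians |
| Blood pressure | Electronic monitor; RA/nurse | Outside clinicians |

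1. If the assessor is a nurse, the first row contradicts the blinding statement. If it is a research assistant (RA), it need not.
2. BMI and blood pressure show the same mismatch between table and text on who measures.
3. Nothing in Outcome measures, Clinical outcomes or Statistical analysis says that a new case means HbA1c of at least 6.5% on a scheduled sample.
4. HbA1c at 6 and 12 months is scheduled for the participants without limit to one cohort or arm, so the data for such a definition would exist.

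**The plan's own figure**

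Inputs from Sample size: incidence 10% and 2%, two-sided 5% level, 90% power, design effects 1.49 and 1.52.

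- Per arm before clustering: n = [1.960 × √(2 × 0.06 × 0.94) + 1.282 × √(0.10 × 0.90 + 0.02 × 0.98)]² / 0.08² ≈ 183.1, rounded up to 184.
- With continuity correction: (183.1/4) × [1 + √(1 + 4/(183.1 × 0.08))]² ≈ 207.4, rounded up to 208.
- 208 × 1.49 × 1.52 = 471.1, the stated 471 per arm.

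This figure reproduces and does not depend on the point raised here. It implies about 471 × 0.10 = 47 and 471 × 0.02 = 9 events, so a few misclassified cases in the low-incidence arm would matter.

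**Illustration only**

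The documents give no detection rates, so those below are assumptions. Observed incidence = true incidence × detection. Effective size is taken as 471/1.52 ≈ 310 per arm, because the 1.52 formula already contains the clustering term. Probabilities come from the normal approximation for two proportions, without continuity correction.

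| True, control / intervention | Detected, control / intervention | Observed, control / intervention | Chance of a significant result in the observed direction |
|---|---|---|---|
| 10% / 10% | equal and complete | 10% / 10% | 2.5% (nominal) |
| 10% / 10% | 90% / 70% | 9% / 7% (ratio 0.78) | about 15% |
| 10% / 10% | 70% / 90% | 7% / 9% (ratio 1.29) | about 15% |
| 10% / 10% | 100% / 50% | 10% / 5% (ratio 0.50) | about 66% |
| 10% / 10% | 50% / 100% | 5% / 10% (ratio 2.0) | about 66% |
| 10% / 2% | equal and complete | 10% / 2% | about 99% |
| 10% / 2% | 70% / 90% | 7% / 1.8% | about 89% |
| 10% / 2% | 50% / 100% | 5% / 2% | about 53% |

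If the scheduled HbA1c decides every case in both arms, detection is equal and this bias does not arise.

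**The case against.** The strongest reply is that EHR here means the study database. It was built for the trial, and all longitudinal data are entered in it. BMI, which is calculated from scheduled weight and height, carries the same EHR and RA/nurse labels. The incidence row may therefore mean only that a research assistant reads the stored 6- or 12-month HbA1c. Trained nurses work at all 26 sites, not only at intervention sites. The monthly prediabetes meetings are described as lifestyle sessions, and no glucose testing is mentioned there. A condensed article may also leave the working definition to a fuller document.

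Much of this stands. A reader might infer from Table 2 that incidence is not taken from the scheduled HbA1c and so depends on allocation and frequency of contact. The documents do not support that. They state no unscheduled diagnostic route, and they schedule the same test for participants in both arms.

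Two things remain. The article does fix the assessor, and in doing so conflicts with its own blinding statement; a fuller document elsewhere does not remove that conflict. And Table 2 uses blood sample and biochemist where a laboratory result is the outcome, but not in this row, so the benign reading is possible but not stated.

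**Conclusion.** The point holds as an inconsistency with a consequence for a primary outcome. As written, an unblinded nurse may classify incident diabetes, and no sentence ties that outcome to the scheduled HbA1c. Ascertainment could therefore differ between arms.

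It is not shown that ascertainment does differ. No size can be derived from the documents. The tabulated results rest wholly on assumed detection rates and can go in either direction. The planned sample size is unaffected.

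Nor should the scheduled HbA1c be taken as fully masked. Beyond the general statement in Randomization, blinding of laboratory staff is described only for the 5% duplicate samples. Baseline assessment has laboratory work done at each health center, where staff know the site and the site determines the arm.

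**What to change.** - **Definition.** State that incident diabetes means HbA1c of at least 6.5%, the plan's own diagnostic threshold, on the scheduled study sample, in every prediabetes participant in both arms. Keep 12 months as the primary time point, as in Outcome measures. Say explicitly whether a positive 6-month result counts as an event, since a participant above the threshold at 6 months may be below it at 12.
- **Table 2.** Change the row to blood sample and biochemist. Remove the nurse as assessor of this outcome, of blood pressure and of BMI, so that the table agrees with Randomization and Clinical outcomes. If nurses will in fact assess these, correct the blinding statement instead.
- **Other diagnoses.** Report diagnoses recorded outside the scheduled visits only as a supporting analysis.
- **Masking.** Label samples with the participant number and without the arm. Do not require masking to site if the assays stay at the local center; that would need coded or centralised testing, which is a new procedure.

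The cost is one table row, two assessor cells and a short definition. The HbA1c tests and visits are already scheduled, and Trial status says that recruitment has not begun.
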